### Statistical and data analysis

Statistical analysis will be conducted using the latest version of appropriate statistical software (e.g. SPSS or STATA). Analyses involving primary outcomes will be conducted on an intention-to-treat principle using all randomised participants. Missing data will be replaced using multiple imputation. Normality will be assessed using the Shapiro Wilks test. For the primary outcomes of pain and function (numeric pain rating scale and Oswestry Disability Index), data will be compared using analysis of covariance (ANCOVA) to investigate the change from baseline to each of the follow-up points. The baseline measure will be the only covariate used in each analysis.

The IPAQ-7 will be used to determine changes in physical activity from baseline for participants using analysis of covariance at each time point (12, 26 and 52 weeks). The correlation between IPAQ-7 score and change in primary outcomes will be investigated and where appropriate (significant correlations identified) a regression analysis performed. For the secondary outcomes of gluteus medius activity and transversus abdominis thickness, ANCOVA will be used to investigate change from baseline following 12 weeks of the intervention for each variable. The baseline measure will be the only covariate used in each analysis. Cohen’s d will used to calculate effect sizes for both primary and secondary outcomes.

Pearson correlation coefficients will be performed between foot type and the change in primary outcome variables at 12, 26, and 52 weeks. Where significant correlations are found, a regression analysis will then be performed to determine the ability of foot type to predict treatment outcomes.

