### Secondary outcomes

The secondary outcomes will include:(i)Gluteus medius muscle activity from baseline to 12 weeks follow-up;(ii)Transversus abdominis muscle thickness from baseline to 12 weeks follow-up;(iii)correlation between foot type and change in pain and function;(iv)physical activity from baseline to 12, 26, and 52 weeks follow-up;(v)number of hours per day and week the prefabricated orthotic is worn over 12 weeks; and(vi)self-reported adverse events associated with the interventions over 52 weeks.

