### Sample size

The sample size for this trial was calculated to find minimal clinically important change of 2 (s = 2.5) on the numeric pain rating scale [29] with 80% power, a 5% Type I error rate and non-adherence rate of 20%. Numeric pain rating scale was chosen for the calculation instead of the Oswestry Disability Index because it had the smaller effect size and thus would require the larger sample size. The calculation adjusted for non-adherence required a total sample size of 30 per group, therefore a total of 60 participants will be recruited.

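### The physical activity regression is fitted only where an unadjusted correlation is significant, so weak associations carried forward may be overstated and may partly reflect arm or baseline severity

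*Protocol article*

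**What the plan says.** All references are to the protocol article.

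- **The rule in question** (Statistical and data analysis): "The correlation between IPAQ-7 score and change in primary outcomes will be investigated and where appropriate (significant correlations identified) a regression analysis performed". The sentence gives no time points, no content for the regression, and no indication whether the IPAQ-7 score is the baseline value, the follow-up value or the change.
- **Between-arm comparison of activity** (same section): a separate analysis of covariance at 12, 26 and 52 weeks, which does not depend on any significance test.
- **Baseline adjustment** (same section): "The baseline measure will be the only covariate used in each analysis". This follows the ANCOVAs of the primary outcomes and of the muscle outcomes, and is not clearly tied to the activity correlation.
- **A parallel rule for foot type** (same section): "Where significant correlations are found, a regression analysis will then be performed to determine the ability of foot type to predict treatment outcomes". The two-step approach is thus used twice.
- **Status** (Secondary outcomes): the list includes "physical activity from baseline to 12, 26, and 52 weeks follow-up", but not the association between activity and the primary outcomes.
- **Size** (Sample size): the calculation targets a "minimal clinically important change of 2 (s = 2.5) on the numeric pain rating scale" and "required a total sample size of 30 per group, therefore a total of 60 participants will be recruited".

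**The concern.** There are three separate issues.

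1. **Selection by p-value.** If a regression is fitted only after its correlation has passed a significance test, the estimates that reach the regression stage are those that came out large. In a sample of 60 this matters when the true association is weak.
2. **No arm term in the screen.** A simple correlation on the pooled sample cannot contain treatment. If the activity score is measured after randomisation and the orthoses shift both activity and the outcome, part of the correlation is just the difference between arms.
3. **No baseline term in the screen.** The correlation uses change scores alone, whereas the main analyses adjust for baseline. If less active people start with worse pain, activity will correlate with change through baseline severity.

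The Background says that measuring activity may help in understanding the response to orthoses. An association produced by selection, arm or baseline could be misread in that light.

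**Working it through.** **Inputs.** From Sample size: difference 2, SD 2.5, 80% power, 5% type I error, 20% non-adherence, 30 per group. Assumed here because the protocol does not state them: two-sided tests, a Pearson correlation for the screen, and the ranges marked as assumed below.

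**Step 1: reproduce the plan's sample size.** n per arm = 2 × (1.96 + 0.8416)² × 2.5² / 2² = 24.5, rounded up to 25. Then 25 × 1.2 = 30, the stated figure; 25 / 0.8 = 31.25, rounded up to 32, is close to it. N = 60 is therefore used, with 60 × 0.8 = 48 as a variant if 20% contribute no data. The planned pain effect is 2 / 2.5 = 0.8 SD.

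**Step 2: the screening threshold.** Critical |r| = t / √(t² + N − 2), with t the 97.5% point on N − 2 degrees of freedom. This gives 0.254 at N = 60 and 0.285 at N = 48.

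**Step 3: effect of the screen.** Bivariate normal data, 100,000 samples per setting, N = 60, keeping r only if p < 0.05:

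| True r | Passes the screen | Mean r among passes |
|---|---|---|
| 0.1 | 12% | 0.30 |
| 0.2 | 34% | 0.33 |
| 0.3 | 65% | 0.37 |
| 0.4 | 90% | 0.42 |
| 0.5 | 99% | 0.50 |

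Without selection, the mean r for a true 0.2 is 0.198, so the correlation itself is essentially unbiased. At N = 48 a true 0.2 passes 28% of the time, with mean 0.36 among passes.

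**Step 4: arm.** Suppose there is no association within arms, allocation is 1:1, the effect on pain change is dy = 0.8 SD, and the effect on activity is dx (assumed range 0 to 0.8 SD). The pooled correlation is

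r = (dx × dy / 4) / √[(1 + dx²/4)(1 + dy²/4)].

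For example, dx = 0.5 gives 0.10 / √(1.0625 × 1.16) = 0.090. The rejection rates come from 20,000 samples of 30 per arm:

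| dx (SD) | Pooled r | False positives, unadjusted | False positives, arm adjusted |
|---|---|---|---|
| 0 | 0.00 | 4.9% | 4.8% |
| 0.2 | 0.04 | 6.0% | 5.2% |
| 0.5 | 0.09 | 10.4% | 5.0% |
| 0.8 | 0.14 | 18.6% | 4.9% |

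If arm shifts only one of the two variables, the unadjusted rate stays near 5%.

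**Step 5: baseline.** Let activity correlate rb with baseline pain, let pain correlate q between baseline and follow-up with equal SDs, and let activity have no link to follow-up pain given baseline. With change = follow-up − baseline,

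corr(activity, change) = rb(q − 1) / √[2(1 − q)].

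With rb from −0.2 to −0.4 and q from 0.3 to 0.7 (both assumed), this runs from 0.08 (rb = −0.2, q = 0.7) to 0.24 (rb = −0.4, q = 0.3). The top of the range is close to the 0.254 threshold.

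**Step 6: number of screens.** Two outcomes: 1 − 0.95² = 9.8% chance of at least one false pass. Two outcomes at three time points: 1 − 0.95⁶ = 26.5%. Both treat the tests as independent, and the second also assumes time points that the sentence does not give.

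**The case against.** The strongest reply is that the sentence is brief and a critic can read too much into it. Four stronger readings are tempting, and the document supports none of them.

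- **That the regression omits arm and baseline.** Its terms are not described, and an article may leave them to the full plan. Their absence is certain only for the screening correlation, if that is the simple correlation it appears to be.
- **That non-significant correlations will go unreported.** The protocol says the correlation will be investigated, without condition. Only the follow-on regression is conditional.
- **That treatment confounding is certain.** If the IPAQ-7 score is the baseline value, arm cannot have affected it. If it is a later value, arm must affect both activity and the outcome, and the induced correlation is small even with the full 0.8 SD effect on pain.
- **That six tests are planned.** No time points are given for this correlation. Repeated measures of related outcomes in the same people are also unlikely to be independent.

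It is also fair to say that the association is not a listed outcome, that the protocol plans no causal or mediation claim from it, and that the Discussion ties the mechanism question to the muscle measures.

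All of this stands and limits the point. It does not remove it. The dependence of the regression on significance is a stated rule, so a fuller plan that follows it inherits it. Even if that plan adds arm and baseline to the regression, an unadjusted statistic will already have decided which regressions are fitted.

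**Conclusion.** The point holds as a minor one. Regression estimates carried forward may be inflated if the true association is weak: about 0.33 on average for a true r of 0.2 at N = 60, and negligible inflation from about 0.4 to 0.5. It would be wrong to conclude that the reported associations will be inflated and confounded by treatment. Inflation applies only to results kept because they were significant. Confounding by arm needs a post-randomisation score and an effect on both variables, and then amounts to an r of about 0.04 to 0.14 for assumed activity effects of 0.2 to 0.8 SD. The baseline artefact (0.08 to 0.24) rests entirely on assumed correlations, but could be the larger of the two. The chance of at least one false pass is 9.8% for two independent screens, and 26.5% only if three time points are assumed as well.

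Only an exploratory analysis is affected. The primary analyses of pain and function and the randomised comparison of activity stand as planned.

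**What to change.** Replace the two-step rule with one prespecified model. For each primary outcome at each time point (12, 26 and 52 weeks), regress the follow-up score on arm, the baseline score and a named IPAQ-7 measure: baseline activity if it is meant as a predictor, change in activity if a concurrent association is meant. Report the activity coefficient with its 95% confidence interval whatever its p-value, and label the results exploratory and not causal. Make clear that the baseline-only covariate rule governs the ANCOVAs and not this model. Where change in activity is in the model, the arm coefficient should not be presented as the treatment effect.

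The cost is a few sentences of analysis text. It needs no extra data or participants. In the scenarios of step 4, and in those where arm shifts only one variable or neither, including arm kept the false-positive rate at 4.8% to 5.3%.

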## Background

Globally, low back pain (LBP) is the greatest cause of disability and is one of the major contributors to disease burden [1]. Direct costs of back pain have been estimated to be over AU$1 billion, most of which are associated with medical treatment [2]. Further to this, an additional AU$8.15 billion is lost through reduced earnings and decreased productivity both at work and home [2]. Recurrence rates of LBP are high, with up to 44% of LBP sufferers experiencing a return of symptoms within twelve months, and 85% having a recurrence over their life-time [3].

The aetiology of LBP is multifactorial with individual characteristics, psychosocial factors, and occupational demands linked to the development of the condition [3, 4]. Due to the varied nature of LBP, up to 85% of cases are classified as nonspecific [5], with the majority of these lasting for periods of greater than 3 months [6]. In such cases the LBP is referred to as chronic nonspecific LBP. Chronic nonspecific LBP is associated with high levels of pain, disability, depression, and reduced quality of life [7]. The evidence for the extensive range of chronic nonspecific LBP treatments has mixed levels of quality and shows highly variable outcomes [8–10].

Foot orthoses are one of the many treatment options available for chronic nonspecific LBP. The justification for the use of foot orthoses to treat chronic nonspecific LBP is based on several theoretical therapeutic mechanisms. These include reducing excessive or abnormal foot pronation [11, 12], achieving realignment of more proximal structures of the lumbopelvic-hip complex through adjustment of pronated foot posture [13, 14], and to increase the contact area of cavus feet so that shock absorption is improved [14, 15]. However, despite widespread use of this form of therapy, the evidence for the efficacy of this treatment for reducing pain and improving function in chronic nonspecific LBP suffers is limited.

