An alternative mechanism of action of foot orthoses is by influencing muscle activity, with some research demonstrating that this is the case when walking and running [23]. This includes changes to timing and intensity of contraction of muscles of the lower leg and thigh [24], and the superficial muscles of the lower back [25]. However, it is unclear how foot orthoses may have this effect and whether or not it is beneficial [23]. Nevertheless, the potential for proximal muscle activity to be altered with the use of foot orthoses may be significant in the treatment of chronic nonspecific LBP, as this condition is associated with dysfunction of deep trunk muscles such as the transversus abdominis [26], and weakness of hip muscles including gluteus medius [27].

Current evidence regarding the efficacy of foot orthoses for treatment of chronic nonspecific LBP, particularly in the long term, is inconclusive, as is the potential effect of foot orthoses on more proximal hip and trunk muscle function. This randomised controlled trial aims to investigate the effectiveness of prefabricated foot orthoses compared to a placebo intervention on pain and function in people with chronic nonspecific LBP after 12, 26, and 52 weeks. The secondary aims include determining the effect that these interventions have on participants’ gluteus medius muscle activity and transversus abdominis muscle thickness over 12 weeks, and physical activity over 12, 26 and 52 weeks. Additionally, the effectiveness of the interventions on pain and function per foot type (supinated, neutral, or pronated), as well as, intervention adherence and adverse events will also be investigated.

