**Fig. 3 Fig3:**
[figure not shown]
**a** Digital inclinometer position for hip internal and external rotation range of motion. **b** Digital inclinometer position for hamstring range of motion

The FPI will be used to assess foot type (Table 1). The FPI consists of six criteria which are graded on a 5 point scale from − 2 to 2, with the score for each criterion summed to create a total score per foot [40]. Foot type will be categorised according to the following: supinated foot (− 1 to − 12), neutral (0 to 5), and pronated (6 to 12) [52].

Skin over the right gluteus medius muscle will be prepared according to the surface electromyography for the non-invasive assessment of muscles (SENIAM) guidelines and a wireless electromyographic sensor (Delsys Trigno™) adhered parallel to the direction of muscle fibres, half way between the line from the iliac crest and the greater trochanter [41]. Foot switches will be used to measure gait events and will be adhered to the planter posterior aspect of the calcaneus, the plantar aspect of the 1st and 5th metatarsal heads, and the plantar surface of the interphalangeal joint of the hallux. Electromyographic measurement of the gluteus medius muscle has been shown to be reliable [42, 53].

Transversus abdominis muscle thickness will be measured with a Shenzhen Mindray M5 diagnostic ultrasound machine and Mindray linear transducer (7L4s), in B-mode at 7.5 MHz, positioned adjacent and perpendicular to the abdominal wall, 25 mm antero-medial to the midpoint between the ribs and ilium, on the mid-axillary line and parallel to the transversus abdominis muscle fibres. Thickness measurements will be made at the hyperechoic fascial lines between the superficial and deep edges of the muscle. Ultrasound measurement of the transversus abdominis muscle has been shown to be reliable [46].

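### The aim on effectiveness per foot type is to be answered by correlating foot type with change, which does not estimate how the orthosis effect differs by foot type

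*Protocol article*

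**What the plan says.** All places are in the protocol article.

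- **Aim (Background, last paragraph).** The trial will also investigate "the effectiveness of the interventions on pain and function per foot type (supinated, neutral, or pronated".
- **Outcome (Secondary outcomes, item iii).** This becomes the "correlation between foot type and change in pain and function".
- **Analysis (Statistical and data analysis, last paragraph).** "Pearson correlation coefficients will be performed between foot type and the change in primary outcome variables at 12, 26, and 52 weeks". Then: "Where significant correlations are found, a regression analysis will then be performed to determine the ability of foot type to predict treatment outcomes". The text does not say whether the correlation is pooled over arms or computed within an arm.
- **Primary model (same section).** "The baseline measure will be the only covariate used in each analysis", so the ANCOVA for pain and function carries no foot-type term either.
- **Foot type variable (Clinical measurements, after Fig. 3).** "Foot type will be categorised according to the following: supinated foot", neutral or pronated, by cut-points on the total Foot Posture Index (FPI) score, which is itself numeric.
- **Discussion.** The authors hope that the foot-type proportions seen here will let later studies be powered for the interaction of foot type with foot orthoses. They therefore recognise that quantity, but no analysis in the article estimates it.

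**The concern.** Effectiveness of an intervention within a foot type is a difference between arms among people with that foot type. Whether it varies across types is a treatment-by-foot-type interaction. A correlation of foot type with change contains no contrast between arms.

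Two wrong conclusions are possible. If people with one foot type improve more whatever they are given, the correlation will be significant, and the planned wording invites a report that foot type predicts the outcome of treatment. If the orthoses do help one foot type more than another, the correlation can be near zero, and the regression that might have looked further is never run. The abstract tells clinicians to expect an understanding of whether foot type influences the outcome, so either error could reach practice as advice on whom to fit.

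**Working it through.** **Inputs.** From the article: 30 per arm, 1:1 allocation, and 2 points with SD 2.5 on the numeric pain rating scale (Sample size). Assumed, because the article does not give them: two-sided 5% tests, SD 2.5 as the residual SD of change within arms, the foot-type mix and all slopes.

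**The plan's own figure.** n = 2 × (1.96 + 0.84)² × 2.5² / 2² = 24.5, so 25 per arm, and 25 × 1.2 = 30. The stated 30 per group is reproduced. It concerns the primary comparison and is not disputed here.

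**What each quantity measures.** Let A = 0 or 1 for control or orthosis, F = foot type, and change = b0 + b1·A + b2·F + b3·A·F + error.

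- Orthosis effect at foot type F, which the aim asks for: b1 + b3·F
- Slope behind a pooled 1:1 correlation: b2 + b3/2
- Slope behind a correlation in the orthosis arm only: b2 + b3

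If b3 = 0, both correlations still pick up b2, which is pure prognosis. If b2 = −b3/2, the pooled correlation is zero despite modification. If b2 = −b3, the orthosis-arm correlation is zero despite modification. This holds at any sample size.

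**Size on the pain scale.** 6,000 simulated trials per row, N = 60, SD 2.5, foot types coded −1, 0, 1 with an assumed 30/40/30% mix. Entries are the percentage of trials with p < 0.05.

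| Assumed truth | Pearson, pooled | Pearson, orthosis arm | Linear interaction |
|---|---|---|---|
| Prognosis only: slope 1.5 in both arms, effect 2 in every type | 90 | 67 | 5 |
| Effects 0/2/4 by type, opposite slopes in the arms | 4 | 35 | 63 |
| Effects 0/2/4 by type, slope in control arm only | 54 | 5 | 63 |
| Slope 1.5 in orthosis arm only, effects 0.5/2/3.5 | 35 | 66 | 40 |
| Effect 3 in supinated and pronated, 0 in neutral | 6 | 5 | 5 |

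In the last row, an interaction test on three categories reaches 47%.

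**Dependence on the assumed slope.** With a standardised FPI score and outcome, 30 per arm:

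- Prognosis only, slopes 0.1, 0.2 and 0.375: pooled Pearson significant in about 12%, 34% and 80%; interaction about 5% throughout. A slope of 0.375 corresponds to r = 0.375/√(1 + 0.375²) = 0.35 within an arm.
- Opposite slopes of 0.4: pooled Pearson about 6%, interaction 83%.
- Slope of 0.8 in controls only: orthosis-arm Pearson 5%, interaction 82%.
- Slope of 0.5 in the orthosis arm only: pooled Pearson 40–44%, interaction about 45%.

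**What the right quantity can deliver at N = 60.** For two foot-type groups with share p in one of them, SE of the interaction = 2.5 × √(2/(30p) + 2/(30(1−p))).

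- p = 0.5: SE 1.29, 95% CI half-width 1.96 × 1.29 = 2.5 points, power 34% for a 2-point difference in effect
- p = 0.2: SE 1.61, half-width 1.96 × 1.61 = 3.2 points, power 24%

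The difference detectable with 80% power is 2.80 × SE, so 3.6 to 4.5 points. For 2 points, about 197 participants would be needed at p = 0.5 and 234 at p = 0.3.

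**The case against.** The best defence is that the analysis matches the outcome as defined: item (iii) is a correlation, and a correlation is planned. The abstract and the closing paragraph of the Discussion speak only of the influence of foot type, which can mean prognosis, and adequate power for the interaction is openly left to later trials. This limits the weight of the point but does not remove it. Item (iii) then fails to serve the Background aim, and the article still contradicts itself.

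Several stronger readings are tempting, but the article does not support them.

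- *A false claim is likely.* The 80% figure needs a prognostic slope that the article does not report; at a slope of 0.1 the figure is 12%.
- *Real modification will generally be missed.* If foot type matters only among orthosis wearers, which is the case closest to the article's premise of an inert booklet, the pooled correlation and the interaction test have similar power. The correlation still cannot say which explanation applies.
- *The protocol expects benefit at both ends of the foot-type scale.* The Background lists theoretical mechanisms, among them "to increase the contact area of cavus feet so that shock absorption is improved" beside the control of pronation. The Discussion calls the effect in types other than pronated unknown. A U-shape is plausible, but it is not predicted.
- *Pearson is invalid for three categories.* A numeric FPI total exists and may be what is meant. This is an ambiguity.
- *Only selected, inflated results will be reported.* The correlations are planned at all three times. Only the regression is conditional, and nothing says that null coefficients will be withheld.
- *The regression has no treatment term.* Its predictors are not listed and may be given in a fuller document. What the article does fix is that it is opened by the wrong test.
- *The physical activity analysis has the same fault.* It has a similar gate ("where appropriate (significant correlations identified) a regression analysis performed"), but it does not concern foot type and gives no time points for those correlations. It is a separate matter.

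**Conclusion.** The point holds as a mismatch between a stated aim and the analysis fixed for it. The algebra alone shows that neither a pooled nor an orthosis-arm correlation identifies the difference in orthosis effect between foot types. The baseline-only ANCOVA does not fill the gap.

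How often this would mislead depends on slopes and a foot-type mix that had to be assumed, so the percentages are illustrations across a range and not forecasts for this trial.

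This is a secondary, exploratory question. It should be corrected before analysis, but it does not threaten the comparison of pain and function between arms.

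**What to change.** Choose one of two routes.

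1. **Keep the aim and change the analysis.** For each primary outcome at 12 weeks, fit an ANCOVA with arm, baseline value, foot type and arm × foot type. In the main model use either the three categories, or FPI with linear and quadratic terms and the product of each with arm. A linear product alone would miss a benefit at both ends as badly as the correlation does. Report the arm difference for supinated, neutral and pronated feet with 95% CIs whatever the p-value. Drop the significance gate, label the analysis exploratory, and treat 26 and 52 weeks as supportive.
2. **Keep the analysis and change the aim.** Reword the Background sentence and the phrase about predicting treatment outcomes as a prognostic question, and make no claim that the orthoses work better in one foot type than another.

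Both routes change wording only, since FPI is already measured at baseline. The cost of the first is wide intervals, and sparse cells if one foot type is rare. That is what 60 participants can support.

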**Discussion:**

This trial will primarily evaluate the effectiveness of prefabricated foot orthotic devices for reducing pain and improving function in people with chronic nonspecific low back pain over 52 weeks. It is expected that this study will provide clinicians and researchers with an understanding of the role that prefabricated foot orthoses may have in the treatment of chronic nonspecific low back pain and a potential mechanism of action, and whether foot type influences the outcome.

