It is also anticipated that this trial will help develop an understanding of the proportions of foot types in people with chronic nonspecific LBP, so that future studies can be adequately powered for the interaction between foot type and foot orthoses. Previous research has either not defined participant’s foot type [16], or has focused only on pronated feet [19]. Castro-Mendez and colleagues [19] found a significant effect in favour of foot orthoses for reducing pain in those with chronic nonspecific LBP and pronated feet, however the effect in relation to other foot types is unknown.

This protocol is based on the SPIRIT guidelines [65]. However, given that this trial will use a placebo intervention for the control group, sources of bias associated with this type of design are important to consider. We will attempt to control ascertainment or detection bias [66], by having two levels of participant information statements and consent forms and maintaining allocation concealment. Nevertheless, some participants such as those that know each other, may discuss their interventions outside of the trial and therefore discover the differences. Given that this trial is designed to have a placebo intervention, a ‘no-treatment’ group was not used because of the potential for participants’ results or behaviour to be influenced by resentful demoralisation [66]; however, this may still occur if participants become aware of the different interventions.

Therefore, whilst we have designed the trial to maintain methodological rigour and control for potential sources of bias associated with a placebo control group, there are still some potential limitations. We will not be able to account for a potential placebo effect or prevent participants from undergoing other treatments external to the study, both of which may confound any treatment effects. We will record any external treatment participants undertake to help with the interpretation of the results.

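### The aim is effectiveness per foot type, but the planned correlation of foot type with change contains no stated arm contrast and cannot separate prognosis from a differential orthosis effect

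*Protocol article*

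**What the plan says.** Four places in the protocol article bear on this.

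- **Aim (Background, last paragraph).** Among the further aims is "the effectiveness of the interventions on pain and function per foot type (supinated, neutral, or pronated").
- **Outcome (Secondary outcomes, item iii).** The outcome is defined as "correlation between foot type and change in pain and function". No arm is mentioned.
- **Analysis (Statistical and data analysis, last paragraph).** "Pearson correlation coefficients will be performed between foot type and the change in primary outcome variables at 12, 26, and 52 weeks". Where a correlation is significant, "a regression analysis will then be performed to determine the ability of foot type to predict treatment outcomes". The text does not say whether the correlation is pooled or run by arm, and it lists no terms for the regression.
- **Between-arm model (same section).** For the ANCOVA of pain and function, "The baseline measure will be the only covariate used in each analysis". Foot type therefore does not enter the comparison of the arms.

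The main Discussion mentions the interaction once. It expects the trial to show how common each foot type is, "so that future studies can be adequately powered for the interaction between foot type and foot orthoses".

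**The concern.** In a two-arm superiority trial, effectiveness is the difference between orthoses plus booklet and booklet alone. Effectiveness per foot type therefore asks whether that difference varies with foot type. A correlation of foot type with change answers something else. Pooled over arms, it asks who improves whatever they were given. Within the orthosis arm, it is an uncontrolled before-after association.

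The risk lies in the reading. A significant correlation, followed by a regression said "to determine the ability of foot type to predict treatment outcomes", could be taken as grounds for choosing patients for orthoses by foot type when foot type is only prognostic. In the other direction, a pooled correlation can come out near zero although the orthosis effect does vary, and the significance gate would then end the inquiry.

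**Working it through.** **The plan's own figure.** The sample size was set for the main effect on pain and is not in dispute. With a difference of 2, SD 2.5, 80% power and two-sided 5% (sidedness is not stated), n per arm = 2 × [2.5 × (1.96 + 0.84)/2]² = 24.5, rounded up to 25. Then 25 × 1.2 = 30 per arm, as stated.

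**What the correlation estimates.** Write change = a + d·arm + b·F + g·(arm × F) + error, with F the foot posture score scaled to SD 1 and arm coded 0/1. The aim concerns g.

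- With 1:1 allocation the pooled correlation reflects b + g/2.
- The orthosis-arm correlation reflects b + g.
- Neither isolates g. Both are non-zero when g = 0 and b is not, and the pooled one vanishes when g = −2b.

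**Inputs for the size.** From the Sample size section: 30 per arm and SD 2.5. Assumed, because the documents give no values: the slopes, an arm effect of 1 point, a normally distributed F, and SD 2.5 as the residual SD of change.

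**Arithmetic check, purely prognostic slope of 1 (b = 1, g = 0).**

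- Pooled: the variance of change is 1 + 6.25 + 0.25 = 7.5 (slope, residual, arm effect), so r = 1/√7.5 = 0.365. Fisher's z is 0.383, and 0.383 × √57 = 2.89. Power = Φ(2.89 − 1.96) ≈ 82%.
- Orthosis arm: r = 1/√7.25 = 0.371. Fisher's z is 0.390, and 0.390 × √27 = 2.03. Power = Φ(2.03 − 1.96) ≈ 53%.
- Interaction test: g = 0, so 5% by construction.

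Simulation (several thousand trials per row) agrees. The entries are the share of trials with p < 0.05:

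| Assumed slope: orthosis / booklet arm | Pooled correlation | Orthosis-arm correlation | Interaction test |
|---|---|---|---|
| 0 / 0 | 5% | 5% | 5% |
| 1 / 1 (prognostic only) | 83% | 54% | 5% |
| 0.75 / 0.75 | 60% | 35% | 5% |
| 0.5 / 0.5 | 32% | 18% | 5% |
| 0.25 / 0.25 | 12% | 8% | 5% |
| 1 / −1 (opposed) | 6% | 54% | 83% |
| 0.75 / −0.75 | 6% | 35% | 59% |
| 1 / 0 (orthosis arm only) | 31% | 54% | 31% |

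In the orthosis-arm column, the rows 1 / 1, 1 / −1 and 1 / 0 all give 54%. That correlation cannot tell pure prognosis from either form of effect modification.

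**Precision of an interaction estimate.**

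- Continuous score: SE(g) = 2.5 × √(1/30 + 1/30) = 0.65 points per SD, so the 95% CI is about ±1.3 points.
- Two equal foot-type groups (a simplification of the three categories), 60 analysed: SE = 2.5 × √(16/60) = 1.29. The difference detectable at 80% power is 2.80 × 1.29 = 3.6 points, and power for a 2-point difference in effect is 34%.
- The same with 48 analysed (60 × 0.8): SE 1.44, detectable difference 4.0 points, power 28%.
- A 2-point interaction at 80% power would need 16 × [2.5 × 2.80/2]² ≈ 197 analysed.

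**The case against.** The best defence is that the analysis matches the outcome as defined. Secondary outcomes item iii and the Abstract both name a correlation, and the closing paragraph of the main Discussion speaks of the influence of foot type on the primary outcomes. On those passages an association is all that is intended, and the mismatch rests on the Background aim. This stands in part. It means that one stated aim goes unanswered, not that every mention of foot type is wrong.

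Three stronger readings are tempting, and the document does not support them.

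- *The Abstract and the analysis section promise an interaction.* They do not. "whether foot type influences the outcome" and "to determine the ability of foot type to predict treatment outcomes" can both be read prognostically.
- *The trial fails to deliver an interaction estimate for planning later trials.* The Discussion offers only the proportions of foot types for that purpose, and the baseline foot posture data supply them.
- *The planned correlation generally misses effect modification.* That holds for the pooled correlation when slopes oppose, an extreme case: at 1 / −1 the orthosis effect shifts by 4 points between −1 and +1 SD of foot posture, twice the 2-point minimal clinically important difference. With a slope in the orthosis arm only, which is closer to the protocol's premise that the booklet does little, the pooled correlation is significant about as often as the interaction test. It still cannot tell that case from prognosis.

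It is also fair to say that the regression is loosely worded and that an analysis plan not shown here could add an arm term. But the article fixes the correlation as the gate, and that gate is the wrong screen for the aim. Finally, an interaction test has little power here. That argues for calling it exploratory, not for estimating a different quantity.

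**Conclusion.** The concern holds in this form: the Background states a treatment-effect aim for foot type, and the stated method cannot answer it, pooled or within arm. The argument does not depend on the simulation settings. The size does: if foot type is prognostic only, the planned screen would be significant in about 12% (pooled, 0.25 points per SD) to 83% (pooled, 1 point per SD) of trials, while the interaction test stays near 5%. The slopes, the normal foot posture score and the use of SD 2.5 for change are assumptions. The point concerns one of six secondary outcomes. The primary comparison, the sample size and the data collection are untouched. It should be corrected, but the trial does not hang on it.

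**What to change.** In Statistical and data analysis, and correspondingly in Secondary outcomes item iii, replace the significance-gated Pearson screen with the planned ANCOVA for pain and function (arm plus baseline value), extended by the baseline Foot Posture Index score and its product with arm. Fit it at 12 weeks and, as support, at 26 and 52 weeks. State that this exploratory model is an exception to the baseline-only covariate rule, which stays in force for the primary analysis.

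Report the interaction estimate with its 95% CI, labelled exploratory. Give the arm differences for supinated, neutral and pronated feet descriptively, since some cells may be small. If a correlation with change is still shown, call it a prognostic association and draw no conclusion from it about who benefits from orthoses.

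The cost is a rewritten paragraph and one outcome line. Foot posture is already measured at baseline, so no new data or participants are needed. The drawback is an imprecise estimate, about ±1.3 pain points per SD of foot posture on the assumptions above, and the report should say so.
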